## Abstract

**Background:**

Affective disorders are associated with an enormous disease burden, necessitating research on the mechanisms of effective treatments.

**Objectives:**

This article introduces the intervention projects of the transregional Collaborative Research Center 393 (CRC/TRR 393). By employing targeted interventions, we aim to induce modifiability in the key mechanisms underlying the trajectories of affective disorders studied in CRC/TRR 393: emotion regulation, expectation, social cognition, and (circadian) cognitive–behavioral rhythms.

**Materials and methods:**

The longitudinal design of the CRC/TRR 393 study will examine four interventions targeting specific mechanisms in subgroups of the German Mental Health Cohort (GEMCO). GEMCO includes patients with a current or lifetime diagnosis of major depressive disorder (MDD), bipolar disorder (BD), and healthy control (HC) participants. Multilevel measurements of these targeted mechanisms will allow us to investigate their fine-grained modifiability and their effects on disease trajectories.

**Results:**

The results will provide insights into how these mechanisms can be modified. Together with the CRC/TRR 393 mechanisms projects, we will examine the effects of key cognitive–emotional mechanisms on disease trajectories.

**Conclusion:**

For the first time, the modifiability of four key mechanisms underlying the trajectories of affective disorders will be investigated both cross-sectionally and longitudinally.

**Supplementary Information:**

The online version of this article (10.1007/s00115-025-01929-0) contains an additional table.

## Introduction

According to German S3 guidelines on the treatment of unipolar and bipolar disorders, first-line treatment for affective disorders comprises psychotherapy and/or psychopharmacological treatment for unipolar depression, depending on the severity [1, 2], and psychopharmacological treatment combined with psychotherapy for bipolar disorder (BD; [2]). However, only up to one third (20–30%) of patients affected by major depressive disorder (MDD) in Germany are treated with psychotherapy [3], and only about half of these patients receive adequate treatment [4]. Additionally, more than 50% of patients with MDD do not respond to evidence-based psychotherapeutic treatment [5], and most treatment studies only have up to 1‑year follow-up assessments and are thus not suitable for investigating the long-term impact of treatment on disease trajectories.

Trajectories of affective disorders are dynamic, with recurrence reported in more than 50% of cases of MDD within 5 years [6] and up to 60% recurrence within 1 year following an initial (hypo-)manic episode in BD [7, 8]. Investigating the key mechanisms associated with these symptom changes holds great promise for improving our understanding of the course and maintenance of affective disorders (see [9]).

The transregional Collaborative Research Center 393 (CRC/TRR 393) study aims to investigate comprehensively the trajectories of affective disorders in a sample comprising patients with current or lifetime MDD, patients with BD, and healthy control (HC) participants, collectively known as the German Mental Health Cohort (GEMCO; for more details, see [10–12]).

Within this framework we investigate the effect of interventions targeting key mechanisms underlying the trajectories of affective disorders [9, 13]: emotion regulation (affective), expectation (cognitive), social cognition (behavioral), and circadian rhythms (physical). The four key mechanisms are not separate from each other but are interconnected and together contribute to symptom fluctuations, recurrences, remissions, and overall disease course. They have all been studied largely in isolation, but there is evidence of interactions between them (e.g., [14–16]), underscoring the importance of integrated investigation.

We take advantage of the longitudinal design and the tandem mechanistic projects [9] focused on specific mechanisms and their modifiability. Together with the interdisciplinary group of researchers involved in CRC 393, this enables a multilevel investigation [10]. Studying the effects of modifiability in these mechanisms on disease trajectories provides the opportunity to draw much stronger, even causal claims about their role in affective disorders. Finally, finding ways to modulate the four targeted key mechanisms will pave the way for the evidence-based development of innovative treatment options. In this funding period, we aim to investigate each intervention with a focus on the modifiability of the targeted key mechanisms. However, the joint research program previously described by Kircher et al. [10] will already enable us to delineate specific hypotheses regarding their interconnection and provide preliminary insights into options for personalized treatment selection. For follow-up research, applying adaptive trial designs offers a way to optimize the set of interventions within a modular treatment approach.

Here, we provide a comprehensive overview of the intervention projects (see also Table e1 in the online supplement) that are conducted within the framework of CRC/TRR 393.

## Cognitive reappraisal-based emotion regulation training (project C01)

Emotion regulation has been extensively investigated in the context of affective disorders (for a review, see [17]). Research indicates that individuals with depression, in particular, demonstrate a narrow repertoire of emotion regulation strategies and encounter difficulties in selecting strategies that are appropriate to the individual context [18]. One of the most widely investigated (and health-promoting) emotion regulation strategies is cognitive reappraisal (CR). This strategy involves reframing one’s thoughts in emotional situations [19] and can modulate emotional responses through goal-dependent evaluations of the situation or the stimulus. Cognitive reappraisal strategies include psychological distancing (e.g., “From an outside perspective, everything looks organized, and in a few weeks, this will feel manageable”) and reinterpretation (“This is one of the best hospitals; the operation will likely go well”), both of which reduce negative affect [20].

In our proof-of-concept study focusing on CR-based emotion regulation training (CR-ERT) in patients with current or remitted depression from GEMCO, patients will be randomized to either an 8‑week CR-ERT or an active control condition. The impact of the CR-ERT on ER flexibility will be assessed in two ways: firstly, behaviorally (via intensive ecological momentary assessment); and secondly, neurobiologically, using pre- and post-intervention multimodal assessments as described in the related mechanism project (see [9]). The role of childhood maltreatment as a risk factor for ER difficulties will also be examined. The study protocol and outcomes have been preregistered in the German Clinical Trials Register (DRKS00036315).

The CR-ERT will be delivered as a digital training program via a smartphone application. Participants will receive weekly 10-min videos introducing a CR technique, along with a daily workbook for practice. The CR techniques comprise the following:*Probability overestimation:* identifying and testing distressing thoughts for exaggerated probabilities*Catastrophic thinking:* exploring catastrophic thoughts by mentally following them to their logical conclusion*Perspective taking:* practicing third-person observation of distressing situations*Distancing:* learning that thoughts are not facts, using metaphors (e.g., a stable mountain vs. a storm) to cultivate detached mindfulness

The active control group will complete cognitive exercises targeting attention, verbal and executive functioning, and spatial perception, accompanied by instructional videos and daily workbook tasks.

We hypothesize that CR-ERT, compared to the control condition, will enhance ER flexibility by broadening the strategy repertoire and improving context-sensitive and adequate strategy selection. These behavioral improvements are expected to be reflected in neural changes in the underlying neural emotion-processing systems. Primary outcomes comprise several data levels, such as changes in ER flexibility (ER choice sensitivity and variability from baseline to follow-up) derived from the intense sampling measures of ERT compared to the control group (also: passive control). Additionally, magnetic resonance imaging (MRI) is used to assess structural plasticity (frontolimbic brain regions) and functional brain plasticity in ER and emotion perception networks between baseline and follow-up in C01, including structural and functional connectivity measures, derived from the ER choice and emotion perception paradigm (B01, [9]) and the ER paradigm (S02, [21]) for the GEMCO cohort. We further aim to explore whether targeting ER flexibility will also improve clinical outcomes (change in the number and frequency of inflection signals/depressive episodes) of participating patients with affective disorders.

## Expectation violation and reward sensitivity as targets in psychological interventions (project C02)

Expectation plays a crucial role in the development and maintenance of affective disorders [22]. In acute depression, individuals often hold negative expectations and beliefs about themselves and the future. In depression, reduced reward sensitivity often prevents positive experiences from updating negative expectations [23]. Only few interventions directly address expectancy violation and reward sensitivity. Patients with depression show blunted psychological and neural responses to rewards, such as monetary gains in gaming tasks [24]. In a randomized clinical trial focusing on reward sensitivity, short-term and long-term analyses demonstrated that improvements in reward sensitivity were most accurately predicted by changes in depressive expectations [25]. Therefore, we hypothesize that an approach focusing on expectation violation will be more effective than an intervention that exclusively focuses on reward sensitivity. Importantly, expectancy violations alone may not automatically lead to expectation change—reward sensitivity can modulate whether expectancy violations alter beliefs.

In the present study, 150 patients with acute MDD from GEMCO and associated outpatient clinics will be randomized into three arms: expectation-focused treatment, reward sensitivity-focused treatment (active control), and a waiting list control. The treatment will be administered by psychotherapists in training in face-to-face group settings over a period of 5 weeks, comprising 10 sessions, with two sessions held per a week. Assessments will be conducted at baseline, post-treatment, and at 6‑ and 12-month follow-ups. The primary objective of these assessments is to measure changes in expectation- and reward-related processes at behavioral and neural levels.

In the *expectation-focused* treatment arm, patients explore their dysfunctional expectations and their role in maintaining depressed mood, and they specify them for testable predictions. Based on this, patients engage in behavioral experiments designed to challenge these expectations. Participants are instructed to maintain daily diaries, integrating experiences from everyday life into therapy (see [26]).

In the *reward sensitivity-focused* treatment arm, patients are introduced to the concept of reward sensitivity and its role in depression. Positive events will be triggered to enhance the psychological effects of positive experiences, thereby also including some strategies from mindfulness-based treatments. The focus of the program will be on (a) increasing sensitivity for the detection of reinforcing events, (b) attention-focusing and perception amplification strategies for positive events, and (c) cognitive appraisal strategies for positive events (adapted version from [27]). As in the expectation-focused arm, diaries will be used to deliver the material to work with in therapy sessions.

In the *waiting list arm,* participants will either wait for treatment or continue any ongoing treatments, but they will not receive additional depression-specific interventions during the study period. Sample sizes and effect sizes are based on earlier mechanism-centered interventions focusing on reward sensitivity and on behavioral activation programs (e.g., [25]), with *d* = 0.3 as a minimum effect size of interest. The primary outcome measures comprise changes in Hamilton Rating Sclae for Depression (HAMD) [28] and MRI-based parameters derived from mechanism-specific paradigms (fMRI), with insula region of interest (ROI) and dorsolateral prefrontal cortex (dlPFC) changes in task-based activation post- vs. pre-treatment. Further, we anticipate both active treatments to outperform the waiting list approach in reducing depressive symptoms. The expectation-focused intervention is hypothesized to be more effective than the reward-sensitivity intervention. Additionally, different neural changes are expected in the active treatment groups, reflecting their targeted mechanisms.

## Positive social affect training (project C03)

Humans are inherently social beings, and social distress plays a significant role in the development and maintenance of affective disorders [29]. Research suggests that social stress transmission—defined as the process by which another person’s stress affects one’s own well-being (i.e., empathic distress)—may be a key mechanism linking social distress to depression [30]. Building on this concept, we will evaluate the effectiveness of *positive social affect training* (PSAT) in patients with depression and their intimate partners, compared to a mindfulness-based active control. The PSAT targets coping with a partner’s stress and alleviating empathic stress. The impact of partners’ recent stressful events, which may cause empathic distress in patients, will also be examined. A total of 100 patients with MDD who are currently euthymic and 100 HC participants from the GEMCO cohort and their partners (*n* = 400 in total) will participate in the study. Half of the dyads will receive an 8‑week PSAT, while the other half will engage in a matched, non-social mindfulness-based intervention. Previous studies that used similar social interaction tasks in healthy individuals showed effects of approximately *d* = 0.3 on behavioral data of empathic affect and affective capacities [31]. The study protocol and outcomes have been preregistered in the German Clinical Trials Register (DRKS00037543).

Both intervention conditions will take place for 8 weeks and will mainly be provided via an app. However, an open session for questions will be held weekly, alongside mandatory online meetings with the trained researcher at baseline and after 4 and 8 weeks of intervention. During the whole intervention, training performance will be assessed via ecological momentary assessment (EMA).

The PSAT targets the reduction in negative empathic affect transmission between partners through two daily exercises that are practiced by the dyads together. The intervention consists of two highly structured mental training exercises: *compassion-focused meditation* (core exercise 1) and *emotion-focused dialogue* (core exercise 2). The exercises last 10 min each and are practiced a minimum of 5 days per week during the intervention period.

The *meditation* fosters positive, caring emotions toward the self and others. Partners engage in meditation in unison, with a focus on themselves, guided by online instructions and audio scripts. This practice has been shown to enhance interpersonal connectedness and to reduce depressive symptoms [32].

The *emotion-focused dialogue* aims to improve empathy and compassion in face-to-face communication. Partners are seated together (or a video call is used if they are apart) and each of them speaks for 2.5 min about a difficult emotional event from the past 24 h, followed by 2.5 min discussing an event from the past 24 h for which they feel grateful. The listener is instructed to maintain compassionate attention without interrupting. Then, the roles are reversed.

This dialogue fosters nonjudgmental acceptance and mutual understanding [33].

The structurally equivalent control condition is a non-social mindfulness intervention, practiced individually without partner involvement, which consists of two core exercises of 10 min duration each: *mindful body scan* and *mindful breathing*. These exercises are widely used in meditation training programs such as mindfulness-based stress reduction (MBSR). This type of mindfulness-based meditation has been confirmed to have specific effects on well-being but not on compassion or related constructs [31]. During the *body scan*, participants systematically direct their attention to different body parts, enhancing interoceptive awareness (for more information, see [34]).

In the *mindful breathing exercise*, participants are instructed to deliberately concentrate on their breathing, without attempting to control it. It has been proven to train participants to intentionally focus attention, maintain stable attention toward a specific focus, and redirect attention when distraction or mind-wandering occurs [35].

We hypothesize that, compared to the mindfulness control, the PSAT will improve social interaction quality, reduce empathic distress, and enhance socio-affective capacities on neural, behavioral, and biological levels [36, 37]. Thus, the primary outcome will be changes in self-reported empathy assessed during the EmpaTom—an experimental task to assess empathy. Additionally, we expect long-term reductions in depressive symptoms, supporting the PSAT as a preventive and therapeutic strategy in depression [38]. Effects on (subclinical) depressive symptoms will be assessed over a 24-month follow-up.

## Circadian rhythms—a randomized dose–response study of wake therapy (project C04)

There is a strong, bidirectional relationship between symptom changes and alterations in cognitive–behavioral circadian rhythms in patients with affective disorders (e.g., sleep). Chronotherapeutic treatments—such as wake therapy—have demonstrated therapeutic efficacy in treating episodes of depression in MDD and BD, despite uncertainties regarding the precise causal mechanism of symptom change [39]. Current models suggest that disrupted neuroplasticity in the left dlPFC during episodes of depression may be a relevant contributing factor. We aim to refine this model by investigating the specific role of rapid eye movement (REM) sleep in relation to mood and neuroplasticity. To this end, we will study 63 patients with unipolar and bipolar depression, currently depressed, using electroencephalography (EEG) and transcranial magnetic stimulation-EEG (TMS-EEG), applying partial wake therapy as a model for inducing rapid and controlled symptom changes. A randomized dose–response protocol will assess the effects of curtailed sleep, aiming to reduce varying amounts of REM sleep, on synaptic density in critical cortical regions and relate this to symptom change.

The indices of neuroplasticity will be derived from TMS-EEG responses and the non-periodic (1/f) component of resting-state EEG.

This 4‑day intervention will investigate neuroplasticity, REM sleep regulation, and antidepressant response to sleep curtailment under tightly controlled circadian and behavioral conditions. The design is informed by robust evidence that REM disinhibition (shortened REM latency, increased REM density) and potentially altered synaptic downscaling during sleep are trait markers of affective disorders and may predict clinical trajectories [40].

Participants initially screened as outpatients will be admitted during the intervention to ensure protocol adherence. The intervention will be administered by trained researchers. The primary objective of this study is to reduce varying amounts of REM sleep and evaluate the impact on density in critical brain regions such as the dlPFC as quantified with EEG and TMS-EEG.

Chronotype will be assessed using the ultra-short version of the Munich ChronoType Questionnaire (μMCTQ). Participants will begin a controlled schedule with fixed wake/sleep times and scheduled light exposure. Resting-state EEG (2 h post-wake and nocturnal recordings) and TMS-EEG will be recorded, alongside measurements of brain-derived neurotrophic factor (BDNF) and assessments with the Montgomery–Åsberg Depression Rating Scale (MADRS), which will be conducted several times. Participants will be blinded to group allocation until wake time. During enforced wakefulness (dim light, 10 lx), quiet activities will be permitted, and adherence will be monitored.

Based on previous sleep deprivation studies, the design has sufficient power (*N* = 63, 80% power, α = 0.05) to detect a medium effect size (*f*^2^ ≈ 0.23) linking REM curtailment to neuroplasticity changes. The primary outcome is the modulation of synaptic plasticity in the left dlPFC, which is quantified using TMS-evoked EEG responses. This is complemented by resting-state EEG aperiodic slope and theta power, which are indices of excitation–inhibition balance and synaptic strength, respectively. Secondary outcomes include detailed REM sleep architecture (latency, density, %REM), serum levels of mature BDNF and proBDNF as molecular markers of plasticity, and acute mood changes, as measured with the MADRS. We hypothesize that baseline REM disinhibition and reduced EEG aperiodic slope during REM reflect trait vulnerability, as previously observed in both MDD and BD. We further expect that the extent of overnight synaptic downscaling, as indicated by steeper post-intervention EEG aperiodic slopes and changes in TMS-evoked potentials, will serve as a predictor of both acute mood response and risk of relapse. Integrating EEG and TMS-EEG metrics with BDNF trajectories provides a multimodal framework for characterizing the antidepressant mechanisms underlying chronotherapy. This is consistent with ENIGMA and EEG literature showing modest but consistent alterations in frontal–limbic circuits and the balance between excitation and inhibition in patients with remitted affective disorders.

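### C04 hypothesises that baseline REM measures reflect trait vulnerability, but a sample of only currently depressed patients cannot separate trait from current state

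*Protocol article*

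**What the plan says.** All of this stands in the protocol article, in the section on circadian rhythms (project C04), unless noted.

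- **Sample:** "we will study 63 patients with unipolar and bipolar depression, currently depressed". No other participant group is described for C04.
- **Trait hypothesis:** "baseline REM disinhibition and reduced EEG aperiodic slope during REM reflect trait vulnerability", with a remark that this has been seen before in both MDD and BD. The design rationale earlier in the section already treats REM disinhibition as a trait marker.
- **Prediction hypothesis:** the extent of overnight synaptic downscaling "will serve as a predictor of both acute mood response and risk of relapse".
- **Primary outcome:** "The primary outcome is the modulation of synaptic plasticity in the left dlPFC", measured by TMS-evoked EEG responses. Secondary outcomes include REM architecture, BDNF and proBDNF, and acute MADRS change.
- **Power:** N = 63, "80% power, α = 0.05", for a medium effect (f² about 0.23) "linking REM curtailment to neuroplasticity changes".
- **Supporting literature:** the section closes by pointing to findings in patients with remitted affective disorders.
- **Parent cohort:** the Abstract (Materials and methods) and the Limitations place the interventions in subsamples of GEMCO, a longitudinal cohort with current or lifetime MDD, BD and healthy controls.

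**The concern.** A trait marker is expected to be present when the person is not in an episode. Everyone in the C04 sample is in an episode when the baseline recording is made. An abnormal REM pattern or a reduced slope would then be found whether it marks a lasting vulnerability or only accompanies the current depression. If the hypothesis stays as worded, a baseline abnormality, or a correlation of baseline values with mood response among depressed patients, could be read as support for a trait. The data would not justify that reading. The appeal to remitted samples adds to the risk, because it supplies from outside the very condition that C04 lacks.

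**Working it through.** **1. What the power statement covers.** Inputs from the C04 section: N = 63, f² about 0.23, α = 0.05, power 80%. Assumed: an F test in linear regression with u tested terms, noncentrality λ = f² × N and degrees of freedom u and N − u − 1. The article does not give u.

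- λ = 0.23 × 63 = 14.49.
- With u = 5, the degrees of freedom are 5 and 63 − 5 − 1 = 57. Power is 81.2% and the required N is 62.
- With u = 1, 2, 3, 4 and 6, power at N = 63 is 96.3%, 92.4%, 88.5%, 84.8% and 77.7%.
- With f² = 0.225, which rounds to 0.23, and u = 5, the required N is exactly 63.

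The stated figure therefore reproduces under u = 5, and 80% is reached for any u up to 5. The effect it concerns is that of REM curtailment on neuroplasticity. It does not concern trait status, relapse or a baseline-by-dose interaction.

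**2. What the sample identifies.** Let μ be the mean baseline value in healthy people, T the shift from having the disorder outside an episode (trait), and S the further shift from being in an episode (state). The group means are:

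| Group | Mean | Described for C04? |
|---|---|---|
| Healthy | μ | no |
| Remitted | μ + T | no |
| Currently depressed | μ + T + S | yes, all 63 |

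The contrasts are:

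- remitted − healthy = T
- depressed − remitted = S
- depressed − healthy = T + S

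C04 alone estimates only μ + T + S. A result that is all T and no S looks the same as one that is all S and no T. More patients make the sum more precise but do not divide it.

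**3. Whether variation inside C04 can replace the missing group.** There are two candidates.

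- *Baseline severity.* Relating REM values to MADRS among depressed patients and extrapolating to no symptoms goes outside the observed range and rests on an untested model.
- *Mood change during the study.* The change is induced by curtailing sleep in order to reduce REM. The intervention thus acts directly on the measure proposed as the trait, and recordings made after it are not recordings in untreated remission.

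**4. The statements side by side.** The hypothesis is about a trait, the sample is wholly in episode, and the closing literature is about remission. Only the last concerns people outside an episode, and those people are not C04 participants.

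**The case against.** The strongest reply has three parts.

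*Trait status is partly a premise.* The design rationale takes it from earlier evidence, and neither the primary objective nor the primary outcome concerns it. This is so, and it limits the consequence. But the same section also states it as a hypothesis, and C04 alone cannot test it.

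*GEMCO could supply the comparator.* The cohort includes people with lifetime MDD and healthy controls. This stands as a possibility. The article does not say that such participants receive the same nocturnal EEG. Its silence does not show that they do not, so the conclusion is confined to C04 data taken alone.

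*The article is condensed.* This disposes of some stronger readings. A reader might infer that patients are observed for only four days and that relapse therefore cannot be studied. The text does not support that: four days is the length of the intervention, and GEMCO's longitudinal design could record later episodes. A reader might also count the lack of a relapse definition or endpoint as a defect. The secondary outcomes are introduced as including those listed, and a definition and follow-up schedule are commonly left to the full protocol. The article claims no power for relapse, so a low number of events would not contradict it. Condensation does not remove the mismatch between the trait hypothesis and the sample, because both are stated in the article.

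**Conclusion.** The point holds as a limit on inference. In the described sample of 63 currently depressed patients, trait and state contributions to baseline REM disinhibition and aperiodic slope cannot be separated from C04 data alone, at any sample size. This rests on the C04 section's account of its sample being complete, with no comparator and no recording in remission. It would fall away to the extent that remitted cohort members with the same nocturnal recordings are brought into the analysis.

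The size is moderate. One stated hypothesis is not testable as worded, while the randomised comparison, the primary outcome and the sample size are unaffected. On relapse, the documents support only a request for clarity: the expectation should be marked exploratory and linked to cohort follow-up. They do not support the conclusion that relapse cannot be studied.

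**What to change.** 1. Restate the trait hypothesis: within current depression, baseline REM measures and aperiodic slope during REM are associated with the response to randomised curtailment. Label moderation of the dose effect (the baseline-by-dose interaction) as exploratory.
2. Make no trait claim unless remitted or healthy GEMCO participants with the same nocturnal EEG are named as comparator. Of these, the remitted group is what separates trait from state, with healthy participants as reference. A healthy group alone gives only T + S.
3. Present the findings in remitted patients as background, and say that C04 does not sample that state.
4. Label prediction of relapse as exploratory and say that it draws on GEMCO follow-up.

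**Cost:** wording, and one interaction term on data already planned. The claim becomes narrower. The N = 63 power statement does not cover the interaction. The article gives neither the number of arms nor an expected interaction effect, so its power cannot be worked out from the document. Naming a comparator costs little if the recordings already exist; if they do not, it means new overnight EEG, and dropping the trait claim is the cheaper course.
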